#### Clinical Outcomes and Adverse Events

Major clinical events will be measured for 12 months from the start of treatment. All-cause death, MI, and stroke will be presented as a composite outcome—major adverse cardiac and cerebrovascular events (MACCE)—and also reported separately. All AEs, including those considered related and unrelated to the intervention, will be recorded and reported from the time of randomization for 12 months or until a patient has completed all trial activities.

### Study Setting

The trial aims to recruit 90 patients. All patients will be recruited, treated, and followed up at a single site: The James Cook University Hospital, Middlesbrough, UK. Blood samples will be analyzed at site laboratories and, where specialist equipment and expertise are required, will be transported to the Institute of Genetic Medicine, Newcastle University, UK, for analysis.

### Study Visits and Assessments

Following baseline assessment and initiation of treatment—placebo or TA-65MD—patients in both groups will be followed up at 1 month, 3 months, 6 months, 9 months, and 12 months (see Table 1). At each visit, drug adherence will be assessed and the patient will be evaluated for AEs.

### Inclusion and Exclusion Criteria

Textbox 1 lists the criteria informing the eligibility or exclusion of patients for the trial.

Inclusion and exclusion criteria.Inclusion criteria—patients will be eligible for the trial if they:Provide written informed consentAre male or female, aged 65 years or over, with an index presentation of an acute coronary syndrome (ACS)* within the previous 6 monthsHave successfully completed revascularization** or are being managed medically following ACSHave angiographic evidence of coronary heart disease: at least one major epicardial vessel stenosis ≥70%Are recruited more than 24 hours after presentation with the index ACS event*ACS defined as either a non-ST elevation myocardial infarction (NSTEMI) or ST elevation myocardial infarction (STEMI)**Percutaneous coronary intervention or angioplasty, eligible the following day, or coronary artery bypass grafting, eligible 3 months following surgeryExclusion criteria—patients will be excluded from the trial if they:Have any disorder associated with immunological dysfunction (ie, acute or chronic inflammatory or neoplastic coexisting disease, known positive serology for HIV, or hepatitis)Are clinically unstable (ie, hemodynamically unstable, cardiogenic shock, or unconscious)Have severe, uncontrolled hypertension (blood pressure [BP] >170/110 mmHg or ambulatory BP of 150/95 mmHg)Have a severe comorbidity that has impact on outcome over the next 2 yearsAre taking immunosuppressantsHave a known malignancyCurrently use a nutritional supplement derived from the roots of theAstragalusspeciesHave a previous known substance addictionHave insulin-dependent diabetesAre judged by the investigator that they should not participate in the study, for example, on the basis of previous serious psychiatric illness or are unlikely to comply with study procedures, restrictions, and requirementsHave participated in any other interventional medicinal study in the past 6 months

### Trial Procedures

#### Screening, Recruitment, and Consent of Participants

Potential participants will be identified by the clinical team following admission to hospital with ACS and having agreed to undergo coronary angiography or having already had an angiography that confirms CHD. Patients may also be identified following discharge. Potentially eligible participants will be invited to participate by a delegated member of the study team. The trial will be explained by the clinical research team and, after time for questions, written consent will be sought from the patient. Written informed consent will be obtained prior to any trial specific procedures and prior to randomization. There will be additional consent for storage of blood samples for up to 5 years for future use in ancillary studies. Patients have the right to withdraw from the trial at any time and without providing a reason. With the explicit consent of patients, general practitioners will be informed of their participation.

#### Eligibility Assessment

Following consent, the principal investigator or a subinvestigator on the delegation log will confirm the patient’s eligibility. Patients who do not meet trial eligibility criteria prior to randomization will be considered a *screen failure* and withdrawn from the trial with no further data collected.

#### Randomization

Randomization will be performed using the Sealed Envelope Ltd system with a minimization scheme to ensure patients randomized to each group are comparable at baseline. The minimization scheme will account for (1) gender (male or female), (2) type of ACS (ST elevation myocardial infarction [STEMI] or non-ST elevation myocardial infarction [NSTEMI]), and (3) CD8+ TEMRA (high >45% or low ≤45%) at baseline.

Eligible patients will be randomized by delegated and trained members of the research team at each center using the 24-hour, central, secure, web-based randomization system with concealed allocation. Eligible patients will be randomized in a 1:1 ratio to receive TA-65MD (intervention under study) or placebo (control arm).

#### Blinding

Assignment to either the TA-65MD or placebo groups will be blinded to the patient, treating clinicians, and the clinical research team, including the pharmacy, research nurses, echocardiogram assessors, laboratory staff, and the chief investigator. Blinding will be maintained in the randomization system, the electronic case report forms (eCRFs), and on investigational medicinal product (IMP) labels. All members of the Newcastle Clinical Trial Unit (NCTU) and the statistics team will be blinded, with the exception of the trial data manager to enable reporting to the independent data monitoring committee as appropriate. The IMP will be labeled using a unique identification code, which will be linked to the study randomization system. TA-65MD and its matched placebo will be identical and presented in the same packaging to ensure blinding of the IMP.

#### Unblinding

Unblinding should not occur except in the case of medical emergencies, where the appropriate management of the patient requires the knowledge of the randomization allocation. To avoid unnecessary unblinding, it will be assumed that the patient is on active treatment within the trial. The Sealed Envelope Ltd online web-based randomization service will be used for emergency unblinding. The primary trial analysis will be performed prior to unblinding. All patients will be informed of which arm they were assigned to, once analysis of the trial data is complete.

### Study Intervention

#### Intervention Under Study: TA-65MD

TA-65MD is marketed as a dietary supplement. The active ingredient of TA-65MD is 1.8% CAG, isolated from roots of the *Astragalus* species. The active ingredient has been identified in an empirical screen of traditional Chinese medicine plant extracts and compounds. TA-65MD is an activator of telomerase, an enzyme whose actions protect the ends of chromosomes from shortening associated with repeated cellular replication. Patients allocated to the intervention will be given 8 mg of TA-65MD twice daily.

#### Control Arm: Placebo

The matched placebo has been manufactured to ensure that it is consistent with TA-65MD in appearance, taste and smell, labeling, packaging, and batch number. Patients allocated to the placebo group will be given this twice daily.

### Safety Data

#### Overview

An independent expert panel has determined TA-65MD to be Generally Recognized As Safe (GRAS) for use in a medical food under the provisions of the Federal Food, Drug, and Cosmetic Act, administered by the US Food and Drug Administration. T.A. Sciences, Inc, provided extensive animal and human clinical data to support the status of GRAS. The safety of TA-65MD has been assessed in an observational study of 114 adults over the course of 1 year [30]. At doses up to 50 mg per day there were no AEs reported for TA-65MD. Safety was also assessed in a randomized, placebo-controlled study involving 117 adult volunteers over the course of 1 year, with no toxicities detected in the liver, kidneys, and metabolic functions as assessed by biochemical markers [29]. An anticipated risk for the use of TA-65MD relates to its ability to activate telomerase. This is the subject of scientific conjecture in consideration of its relationship to cancer [31,32]. An in vitro assay testing the telomerase-activating potency of TA-65 (ie, CAG not in capsules) in Medical Research Council cell strain-5 (MRC-5) fibroblasts suggested there was dose-related TA (Sierra Sciences Labs). While telomerase activation has been observed, TA-65MD does not increase the lifespan of cells. In fact, the preliminary observation of a controlled in vivo cancer study using 5 mL/kg of TA-65 (ie, CAG not in capsules) or sham drug administered by oral gavage for up to 40 days in mice xenografted with four different human tumors—lung (H460), colon (HT29), breast (MDA-MB-435), and prostate (PC3)—suggests a trend toward tumor growth retardation in two cancer types; as well, there was no statistically significant adverse effects on body weight or tumor size for any of the cell lines nor on the growth rate of the tumors (internal T.A. Sciences document, 2008). Given that the population under study in the TACTIC trial are elderly with ACS, and that there were no data on the impact of the drug on the outcomes or population, we chose to conduct the trial using a conservative dose of 8 mg twice daily.

#### Known Side Effects

TA-65MD may interfere with medications that suppress the immune system and may also affect blood sugar and blood pressure. In an observational study, two subjects self-reported an “anxious” feeling shortly after voluntarily increasing their daily consumption of TA-65MD to 100 mg/day—a self-imposed choice without physician approval at a consumption level two times above the intended dose for this observational study; the feelings resolved in both subjects when daily consumption was returned to 50 mg/day.

### Administration and Adherence

Participants may begin taking the IMP immediately following the completion of all baseline assessments, confirmation of eligibility, and randomization. A dose of 8 mg of TA-65MD (T.A. Sciences) or matched placebo will be taken as 1 × 8-mg capsule twice daily (ie, morning and evening). Participants will take the allocated IMP until the end of follow-up at 12 months. Patients will be prescribed IMP following randomization and at 1, 3, 6, and 9 months following the start of the intervention. Returned capsules at each visit will be used to calculate the adherence for each participant. Concomitant medications will also be reviewed and documented at each visit.

### Withdrawal of Participants

Participants will be made aware of their right to withdraw from the trial at any time for any reason and without giving a reason. Participants will be withdrawn from the trial by the clinical team for any of the following reasons:

Intercurrent illness means the participant is no longer able to complete study procedures.The patient suffers unacceptable side effects caused by the study drug.Suspected unexpected serious adverse reactions occur.

The investigator can withdraw participants in the event of any reason that would compromise participant safety or the validity of the results. Data and blood samples collected up to the point of withdrawal will be kept and used in the analysis of the trial unless the participant explicitly requests for these to be removed.

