### Pharmacovigilance

All AEs will be recorded in the participants’ medical notes and on the eCRFs. AEs will be recorded from the day of randomization until the last visit or until withdrawal, with the exception of those considered related to the IMP, which will be followed until resolution, a stable outcome, or death. All AEs are assessed for severity, causality, expectedness, and seriousness by an investigator; all are reviewed by the Independent Data Monitoring and Ethics Committee (IDMEC). In accordance with current legislation, AEs will, where necessary, undergo expedited reporting to the sponsor and to the Medicines and Healthcare products Regulatory Agency (MHRA) within the required timelines.

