#### Statistical Analysis

Primary analysis will follow intention-to-treat principles with patient data analyzed according to randomization and irrespective of intervention received; other analysis groups, such as per-protocol groups, may be considered subsequently. Every effort will be made to retain and include all patients who are part of the trial.

Data will be summarized by study group. Mean or median will summarize continuous variables, whereas number and percentage will be used to summarize categorical variables. A general linear model will be used to analyze the primary outcome considering all covariates used in the randomization scheme. Similar methods will be used to analyze all continuous secondary outcomes. Data of other types will be analyzed using generalized linear models with appropriate distributions.

The numbers of MACCE after 12 months will be compared between arms by the use of standardized rates (eg, by consideration of the number of events per patient month in each arm). Impact of missing data will be explored by tabulating the proportion of missing data in each arm. A full statistical analysis plan will be developed for the outcome measures and agreed upon with the IDMEC and the chief investigator prior to any analysis being undertaken.

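### Drug side effects and suspected unexpected serious adverse reactions lead to withdrawal from the trial, with no off-drug follow-up described; this conflicts with the intention-to-treat, retention and 12-month follow-up statements

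*Protocol article*

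**What the plan says.** The Withdrawal of Participants section of the protocol article is worded as a requirement: "Participants will be withdrawn from the trial by the clinical team for any of the following reasons". Three reasons follow:

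- "Intercurrent illness means the participant is no longer able to complete study procedures"
- "The patient suffers unacceptable side effects caused by the study drug"
- "Suspected unexpected serious adverse reactions occur"

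The investigator may also withdraw participants where safety or the validity of the results would be compromised. On data handling the section says "Data and blood samples collected up to the point of withdrawal will be kept and used in the analysis of the trial", unless the participant asks for removal. It says nothing about data after that point.

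The Pharmacovigilance section says "AEs will be recorded from the day of randomization until the last visit or until withdrawal". It makes an exception for events considered related to the study drug, which are followed to an outcome.

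Other sections point the other way:

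- **Statistical Analysis:** the primary analysis is intention-to-treat, with "patient data analyzed according to randomization and irrespective of intervention received", and "Every effort will be made to retain and include all patients who are part of the trial".
- **Statistical Considerations, Overview:** 90 patients are to be recruited and analysed, 45 per group.
- **Primary Outcome:** the arms are compared at 12 months.
- **Clinical Outcomes and Adverse Events:** major clinical events are measured over 12 months from treatment start. Related and unrelated AEs are recorded for 12 months or to the end of the patient's trial activities.

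**The concern.** For side effects and suspected unexpected serious adverse reactions, the text merges two decisions: stopping study drug and leaving the trial. An intention-to-treat comparison depends on observing outcomes in people who stopped treatment as well as in those who stayed on it. If the first decision brings the second with it, the 12-month CD8+ TEMRA value is missing for a group selected by what happened to them on treatment.

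Three things are at stake. The primary estimate could be biased if such removals differ between arms, and the article intends its estimates to inform a larger trial. Deaths, myocardial infarctions and strokes after withdrawal could go uncounted. The AE profile, a named secondary objective, would lose new events and events judged unrelated in the patients who had already had problems.

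This is a data-collection rule. A later analysis plan can choose a missing-data model, but it cannot recover samples and events that were not collected.

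**Working it through.** **1. Sections side by side, for a patient withdrawn for side effects at, say, month 4**

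| Item | Under Withdrawal and Pharmacovigilance | Under the other sections |
|---|---|---|
| 12-month TEMRA | No provision for collection after withdrawal | Needed for the 12-month comparison and for analysing 90 |
| Major clinical events, months 4-12 | No provision | Measured for 12 months |
| Drug-related AE | Followed to an outcome | Recorded |
| New or unrelated AE, months 4-12 | Recording has ended | Recorded for 12 months or to the end of trial activities |

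The last row conflicts less if withdrawal itself counts as the end of a patient's trial activities. The second row has no such reading, because the 12-month event window carries no alternative end point.

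Two other places support reading withdrawal as leaving follow-up. Administration and Adherence has participants taking drug to the end of follow-up and describes no off-drug period. Eligibility Assessment uses the same withdrawal phrase for screen failures and there ends data collection. That second case is before randomization, so it is suggestive only.

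**2. The plan's own figure**

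45 + 45 = 90. The article gives no SD, effect size, power or withdrawal rate, so nothing further can be reproduced and no stated figure is shown to be wrong.

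**3. Precision (withdrawal rates assumed, equal in both arms)**

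The number per arm is n = 45 × (1 − w), rounded down. The 95% half-width in SD units is 1.96 × √(2/n). Planned follow-up is 90 × 12 = 1080 person-months. The loss is 1080 × w × 0.5 if withdrawals are spread evenly over the year.

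| w | Patients with a 12-month value | Half-width (SD) | Person-months lost |
|---|---|---|---|
| 0 | 90 | 0.413 | 0 |
| 5% | 84 | 0.428 | 27 |
| 10% | 80 | 0.438 | 54 |
| 15% | 76 | 0.450 | 81 |
| 20% | 72 | 0.462 | 108 |

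With the t quantile on 88 degrees of freedom, the half-width at 45 per arm is 0.419, so about 0.42 SD.

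**4. Bias (all inputs assumed)**

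Suppose withdrawn patients differ from retained patients by g SD at 12 months, in the same direction in both arms. Dropping them shifts each arm's mean by −w × g, so the difference between arms shifts by −(wA − wP) × g, where wA and wP are the active and placebo withdrawal rates.

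- 15% versus 5%: 0.10 × 0.25 = 0.025 SD, up to 0.10 × 1.0 = 0.10 SD.
- 20% versus 5%: 0.15 × 0.25 = 0.0375 SD, up to 0.15 × 1.0 = 0.15 SD.
- Equal rates: no shift on this simple model.

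If active-arm removals were the more frequent and had higher TEMRA, the shift would favour TA-65MD. If they had lower TEMRA, it would go the other way.

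**The case against.** The strongest defence has five parts.

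- **Intention-to-treat still operates.** Patients are analysed in the arm to which they were randomized, poor adherence is not listed as a reason for withdrawal, and data before withdrawal are used. This stands. A reader might infer that the intention-to-treat analysis cannot be delivered at all, but the documents do not support that. What is lost is the later data of those removed, so the analysis leans on missing-data assumptions, which an analysis plan may set.
- **The illness trigger is conditional.** It applies only when the participant can no longer complete study procedures. This stands. A reader might infer that any intercurrent illness, including an infarction or stroke, forces removal, but the text does not say so. Where it does apply, the 12-month sample may be unobtainable anyway, and mainly event and vital-status follow-up could be gained.
- **Safety capture does not simply stop.** Drug-related events are followed to an outcome, and the clinical outcomes section sets 12-month windows. This stands against any claim that later events are never observed. What remains is that the sections disagree for a withdrawn patient.
- **This is a condensed article.** The full protocol may separate levels of withdrawal, and the absence of that detail is no fault here. The conflict in the printed wording remains.
- **Few patients may be affected.** Safety Data, Overview, reports no AEs at up to 50 mg per day in an observational study of 114 adults over one year. This stands as a reason for caution about size.

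Rates per patient-month, which the article offers for major events, allow for shorter follow-up only if removal is unrelated to risk. Removal for side effects or illness gives no assurance of that.

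**Conclusion.** The conflict is real and lies in the stated text. For unacceptable side effects and suspected unexpected serious adverse reactions, withdrawal is from the trial and no off-drug follow-up is described. That does not fit the retention statement, the plan to analyse 90, the 12-month primary comparison or the 12-month event window.

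Its effect cannot be sized from the documents. Under the assumed unequal withdrawal the bias is 0.025-0.15 SD, at most a little over a third of the half-width (0.15 / 0.42 ≈ 0.36). The withdrawal rates, their imbalance and the SD differences are all assumptions, and the true number removed may be small. The point is therefore a low-cost correction. It does not show that the trial's comparison is invalid.

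**What to change.** Reconcile Withdrawal of Participants, Pharmacovigilance, Clinical Outcomes and Adverse Events, and Statistical Analysis as follows:

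- Define two separate states: stopping study drug, and withdrawing from follow-up.
- State that participants who stop study drug remain in follow-up for the scheduled 6- and 12-month outcome samples, major clinical events and AEs, unless they decline.
- Where illness prevents study procedures, continue at least major-event and vital-status follow-up where possible.
- Align the AE recording window in the two sections that define it.

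The cost is protocol wording, one case report form field, and follow-up visits for patients off drug, which are already in the schedule of assessments. Recruitment ended in March 2020, so the change can help only participants still within their follow-up. Anyone already removed should be reported by arm, with the reason and timing. The change takes no position on when study drug should be stopped.

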### Pharmacovigilance

All AEs will be recorded in the participants’ medical notes and on the eCRFs. AEs will be recorded from the day of randomization until the last visit or until withdrawal, with the exception of those considered related to the IMP, which will be followed until resolution, a stable outcome, or death. All AEs are assessed for severity, causality, expectedness, and seriousness by an investigator; all are reviewed by the Independent Data Monitoring and Ethics Committee (IDMEC). In accordance with current legislation, AEs will, where necessary, undergo expedited reporting to the sponsor and to the Medicines and Healthcare products Regulatory Agency (MHRA) within the required timelines.

### Statistical Considerations

#### Overview

A pragmatic decision was taken to recruit and analyze data on 90 patients: 45 in each group. This sample size is the minimum conventional threshold for making parameter estimates in pilot studies [33]. The parameter estimates in this trial will be used to inform a large, multicenter clinical trial. 

